#### Sample size

No formal sample size calculation is required for a pilot study [51]. To minimise the maximum likely error for any calculated rates to less than 10%, Eldridge et al. [52] suggested a total of 23 clusters for cluster-randomised pilot studies with a cluster size of five participants, assuming an intra-cluster correlation (ICC) of 0.05. Similar ICCs were found for psychological outcomes in German PC [53] and recruiting six patients per PC practice was considered feasible for psychological interventions [54, 55]. To balance scientific considerations and practical constraints (i.e., time and staff resources), a sample size of 100 patients across 20 PC practices is anticipated, with six patients enrolled per practice, accounting for an expected 20% dropout rate. This should provide sufficient data to adequately assess treatment feasibility, acceptability and potential effectiveness, forming a robust basis for a confirmatory main trial.

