**Methods:**

A total of 100 adult patients with a mental health condition will be recruited by general practitioners. In the intervention group, general practitioners will administer the transdiagnostic intervention, introducing patients to psychological concepts based on transdiagnostic factors (i.e., understanding emotions, cognitive flexibility, countering emotion-based avoidance). In the control group, general practitioners will provide improved treatment as usual oriented on official German treatment guidelines for depression, anxiety and somatoform disorders. In both study groups, treatment will be carried out in four 20-min sessions over 12-weeks. Self-report questionnaires will be completed before treatment initiation (only patients) and after treatment completion (patients and general practitioners) to assess feasibility and acceptability (i.e., treatment recruitment, delivery, response, effectiveness, unintended consequences and maintenance) as well as potential effectiveness (i.e., change in transdiagnostic factors).

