## Methods

### Design

The pilot study will adopt a parallel-group, two-arm, cluster randomised controlled design. It adheres to the CONSORT statement extension to randomised pilot and feasibility trials [42] and to the SPIRIT guidelines [43] (Additional file 1). Using a 1:1 allocation ratio on PC practice level, GPs will provide patients with either a transdiagnostic intervention (i.e., intervention group (IG)) adapted from the UP [24], or with iTAU (i.e., control group (CG)) based on official German guidelines for the treatment of a depression, anxiety or somatoform disorder [44–46]. In both study groups, treatment will consist of four 20-min sessions administered over 12 weeks. Data collection will take place at baseline (patients only) and after treatment completion (patients and GPs) (Fig. 1).

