### Population and setting

A total of 100 German adult PC patients with a mental health condition will be recruited by GPs from 20 PC practices within the region of Munich, Germany.

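### The sample size figures do not agree: 100 recruited, six enrolled in each of 20 practices (120), and 20% dropout cannot all hold

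*Protocol article*

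**What the plan says.** The protocol article gives the target in four places.

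- Abstract, Methods: "A total of 100 adult patients with a mental health condition will be recruited by general practitioners".
- Methods, Population and setting: "A total of 100 German adult PC patients with a mental health condition will be recruited by GPs from 20 PC practices".
- Methods, Sample size: "a sample size of 100 patients across 20 PC practices is anticipated, with six patients enrolled per practice", followed by "accounting for an expected 20% dropout rate".
- Discussion, the paragraph on limitations: 100 patients is repeated as the target, without saying whether it counts patients enrolled or patients completing.

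The figure 120 is never written, and no section says outright that 100 is the number after dropout. The Sample size section opens with "No formal sample size calculation is required for a pilot study". It then cites a recommendation of "a total of 23 clusters for cluster-randomised pilot studies with a cluster size of five participants", at an ICC of 0.05, to keep the error of any estimated rate below 10%. It settles on 20 practices for practical reasons.

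**The concern.** The first two places count 100 patients at recruitment, an average of five per practice. The third puts six per practice into the study, which is 120. The article does not distinguish recruitment from enrolment; GPs do both. Two totals are therefore given for what reads as the same quantity. The obvious rescue, that 100 is the number remaining at the end, does not reproduce at the stated dropout rate either.

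What is at stake is how many patients will supply t1 data. Patients' feasibility and acceptability ratings, which are primary outcomes, are collected only at t1 (Primary outcome measures). Dropout before t1 therefore reduces the primary data directly. A reader planning the main trial also needs one planned enrolment and one planned retention figure to compare with what was achieved.

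**Working it through.** **Inputs.** 20 practices, six enrolled per practice, 20% dropout, total 100 and ICC 0.05 (all from Sample size); 100 recruited (Abstract; Population and setting). Allocation is 1:1 by practice (Design), which does not affect the total.

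**Step 1: can 100 be reproduced?**

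- Enrolled = 20 × 6 = 120. This is not 100.
- Remaining after dropout = 120 × (1 − 0.20) = 96, or 4.8 per practice. This is not 100.
- Enrolment needed for 100 remaining = 100 / (1 − 0.20) = 125, or 6.25 per practice. This is not 120.
- Dropout that takes 120 to 100 = 1 − 100/120 = 16.7%. This is not 20%.
- Multiplying instead of dividing: 100 × 1.20 = 120, and per practice 5 × 1.20 = 6. This matches exactly. The likely source of the six is therefore inflation by 1 + d where division by 1 − d was needed. The article does not show its calculation, so this is an inference.

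**Step 2: the possible readings.**

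| Reading of the target | Enrolled | Expected with t1 data |
|---|---|---|
| 100 is the number recruited | 100 (5 per practice) | 100 × 0.80 = 80 |
| Six per practice | 120 | 96 |
| 100 is the number after 20% dropout | 125 (6.25 per practice) | 100 |

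**Step 3: what this does to precision.** Worst-case 95% error for a rate, taken at a proportion of 0.5:

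error = 1.96 × √(0.25 × DE / n), with DE = 1 + (m − 1) × 0.05 and m the mean number analysed per practice.

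Check against the article's benchmark: 23 × 5 = 115, DE = 1.20, error = 1.96 × √(0.25 × 1.20 / 115) = 10.0 points. This agrees, to rounding, with the 10% limit cited, so the formula is a fair stand-in for the one used.

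| n at t1 | m | DE | Pooled error | Error per arm (n/2) |
|---|---|---|---|---|
| 100 | 5 | 1.20 | 10.7 points | 15.2 points |
| 96 | 4.8 | 1.19 | 10.9 points | 15.4 points |
| 80 | 4 | 1.15 | 11.7 points | 16.6 points |

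Going from 100 to 96 costs 0.2 points on a pooled rate; going from 100 to 80 costs 1.0 point.

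**The case against.** The best defence is that the Sample size section explains itself. It ties six per practice to dropout, so 100 is most naturally the number left afterwards. On that reading the shortfall is four completers, or five enrolled, because 6.25 per practice was not rounded up. The section disclaims a formal calculation and calls the figure anticipated. This stands, and it is why the matter is small. It does not remove the conflict with the two places that count 100 at recruitment, and 96 is still not 100.

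A reader might infer more serious harm. The document does not support these inferences:

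- *That a primary outcome is scored against the recruitment target.* The primary outcomes are patients' and GPs' ratings, mostly agreement with statements on a 4-point scale (Primary outcome measures). The Outcomes section sets no definitive threshold for proceeding to a main trial. The number of patients approached is recorded only under Additional outcomes.
- *That recruitment stops at the wrong count.* Data collection and management schedules recruitment by calendar dates. No rule ends it at 100.
- *That a practice can meet one stated target and miss another.* The Abstract gives neither the number of practices nor a per-practice figure. Five is only an average, and the Randomisation section expects practices with more participating GPs to treat more patients.
- *That the analysis is planned on 80.* That figure requires setting aside the explicit six per practice. The mixed models can also use patients with baseline data only, although the t1 ratings cannot.

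**Conclusion.** Wrong as written; minor severity. No reading satisfies 100 recruited, six in each of 20 practices, and 20% dropout together. Depending on the reading, enrolment is 100, 120 or 125 and the expected number with t1 data is 80, 96 or 100. On the most natural reading the discrepancy is 96 against 100, or 10.9 against 10.7 points of worst-case error for a pooled rate. The least favourable reading gives 11.7 points. No power statement, progression threshold or stopping rule changes.

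The precision figures assume a proportion of 0.5, an ICC of 0.05, equal numbers analysed per practice, and that the 20% dropout means no t1 questionnaire. The register entry is not shown, so nothing can be said about whether it agrees.

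**What to change.** State two numbers, labelled as enrolled and as expected at t1, and use them in the Abstract, Population and setting, Sample size and Discussion. The choice is the sponsor's.

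- Keeping six per practice: 120 enrolled (six in each of 20 practices), 96 expected with t1 data after 20% dropout.
- Keeping 100 at t1: 125 enrolled, for example 15 practices with six and five with seven (90 + 35 = 125).
- Keeping 100 as the number recruited: drop six per practice and state that about 80 are expected at t1.

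The first option needs the least change, because it keeps the design in the Sample size section and corrects only the labels and the 100. Check that the register entry agrees with whichever pair is chosen. No recruitment criterion needs to be added. The cost is a few words in four places and, under the first option, planning on 96 patients at t1 where the text now suggests 100.

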### Procedure

Before treatment start, IG and CG practices will receive a two-hour training (t_-1_) in which GPs are informed about the structure and content of the treatment (i.e., transdiagnostic intervention or iTAU). In both study groups, upon obtaining informed consent and before the first treatment session is delivered, patients will complete a baseline questionnaire (t_0_) in their PC practice via tablets using the online platform SoSci Survey [56]. In case of technical problems, a printed version of the baseline questionnaire will be used. No later than 10 days after completion of the baseline questionnaire, participants will receive the first session of their allocated treatment. Over the course of the 12-week treatment, selected study parameters (e.g., treatment fidelity, serious adverse events) of patients will be recorded with a documentation sheet by GPs. After the last (i.e., fourth) treatment session, a post-treatment digital questionnaire (t_1_) will be provided to patients which will again be completed in their PC practice with tablets (alternatively, a printed version will be used). Once the treatment of all patients is completed, GPs will be invited to fill in a digital questionnaire (t_2_). Study participation is free of charge. As compensation and to promote participant retention, participants will receive a 25€ voucher after completion of each questionnaire. GPs will be incentivised with 100€ for each recruited patient.

#### Treatment

Intervention condition: An adapted version of the UP [24] will be administered by GPs to patients. The treatment consists of four 20-min sessions. To facilitate treatment delivery, a table-flipchart was designed, comprising session-specific slides. In session 1, GPs introduce the functional model of emotional processing which identifies negative reactivity to emotions and dysfunctional coping mechanisms as common factors for emotion-based disorders. In addition, the function and composition of emotions are explained. Session 2 addresses the concept of cognitive flexibility. The interrelationship of thoughts and feelings is especially emphasised. Patients will be encouraged to question automatic negative thoughts and to adopt flexibility in their cognitive appraisal. Session 3 focuses on emotion-based avoidance. Different types of emotion-based avoidance are discussed and possible alternative actions are explored to enable an active and constructive processing of undesirable emotions. In session 4, GPs and patients reflect on the course of treatment, summarise major takeaways and discuss further (psychotherapeutic) treatment options, if necessary. To complement the treatment, patients will be given a booklet. After each session, patients will receive a prescription from their GP to complete a corresponding section in the booklet. This involves reading a text (e.g., concept of cognitive flexibility), completing a related task (e.g., reflecting on automatic thoughts during an emotionally stressful situation) and engaging in two enjoyable activities (e.g., taking a walk in nature, talking to a friend).

Control condition: In the CG, iTAU will be delivered. GPs are instructed to align treatment with the official German guidelines for the treatment of a depression, anxiety or somatoform disorder [44–46]. Apart from carrying out four 20-min sessions, no further structure is provided.

#### Risk management

No negative side effects are to be expected for study participants. Patients with a severe mental health condition (e.g., suicidal ideations) will be identified by GPs at study start and provided with the necessary, more specific care. In the event of a serious adverse event, GPs will ensure their patient’s well-being, decide whether continuation in the study is possible and communicate this to the study team.

### Outcomes

Feasibility, acceptability (i.e., primary outcomes) and potential effectiveness (i.e., secondary outcome) will be assessed quantitatively. A digital questionnaire will be answered by patients at baseline (t_0_) and at the end of their treatment (t_1_). GPs will be surveyed after completion of all treatments (t_2_) (Table 1). Due to the uncertainty of estimates in pilot studies, no definitive thresholds were defined for proceeding to a confirmatory main trial [42]. Rather, the decision to proceed will be based on the overall implications of the intervention’s feasibility, acceptability and potential effectiveness, the criteria for which are outlined below.

**Table 1 Tab1:**
[figure not shown]
Schedule of enrolment, treatment and assessments according to SPIRIT

s1, s2, s3, s4 = treatments sessions 1 - 4; GPs = general practitioners; IG = intervention group; CG = control group

#### Primary outcome measures

Feasibility and acceptability of the intervention and control treatment will be evaluated post-treatment (patients: t_1_; GPs: t_2_). Corresponding questionnaires are based on the process evaluation framework for cluster randomised controlled trials of Grant et al. (2013) [57] and a previous similar pilot study conducted in the PC setting [58]. Patients and GPs will be asked to respond to statements on treatment recruitment, delivery, response, effectiveness, unintended consequences and maintenance. Their degree of agreement will be assessed on a 4-point Likert scale (“strongly disagree” to “strongly agree”). Examples of questions for GPs and patients are: recruitment- “Recruited patients did not differ from patients who did not participate”; delivery - “I followed the instructions for implementing the treatment”; response - “The content of the treatment sessions was understandable to me”; effectiveness - “The treatment helps patients to better manage their mental health condition”; unintended consequences - “The treatment did not lead to any undesired consequences for me”; maintenance - “I would recommend the treatment to my colleagues“. For additional questions on the duration and amount/number of treatment sessions, 3-point Likert scales will be used (“too short”, “adequate duration”, “too long”; “too few”, “adequate amount/number”, “too many”, respectively). The overall treatment satisfaction will be monitored in school grades (1: “very good” to 6: “very bad”).

#### Secondary outcome measures

At t_0_ and at t_1_, patients will complete self-report diagnosis-specific and transdiagnostic questionnaires. Potential effectiveness will be based on change in transdiagnostic factors relevant to emotion-based disorders [27, 28], thus serving as surrogate outcomes [42] for patients’ improvement in mental health.

##### Diagnosis-specific outcomes

Patient Health Questionnaire-9 (PHQ-9): The PHQ-9 [59] assesses the occurrence of depressive symptoms over the last two weeks with nine items rated on a 4-point Likert scale (0: “not at all present” to 3: “present nearly every day”). The total score can range from 0 (no depression) to 27, with larger scores being indicative of greater dysfunction. Cut-offs of ≥ 5, ≥ 10, ≥ 15 and ≥ 20 can be applied to differentiate between a mild, moderate, moderately severe and severe form of depression. The German PHQ-9 was shown to have satisfactory internal consistency (α = 0.89) in a PC sample as well as to fulfil construct and criterion validity [59].

Generalised Anxiety Disorder Screener‐7 (GAD-7): The GAD-7 [60] is a 7-item scale to measure general anxiety symptoms within the past two weeks on a 4-point Likert scale (0: “not at all present” to 3: “present nearly every day”). Total scores can range from 0 (no anxiety) to 21. A larger score represents a more severe impairment. Mild, moderate and severe anxiety symptoms are associated with a score of ≥ 5, ≥ 10 and ≥ 15, respectively. In a representative sample of the German population, the internal consistency of the GAD-7 was found to be satisfactory (α = 0.89) and its construct validity has been shown [60].

Patient Health Questionnaire-15 (PHQ-15): The PHQ-15 [61] uses 15 items rated on a 3-point Likert scale (0: “not bothered at all” to 2: “bothered a lot”) to determine somatic symptom severity experienced over the last four weeks. The sum score can vary between 0 (no somatic symptoms) and 30. Higher values correspond with an increased probability of suffering from a somatoform disorder. Cut-off points for low, medium and high somatic symptom severity were established for values ≥ 5, ≥ 10 and ≥ 15. The internal consistency (α = 0.80) as well as convergent and discriminant validity of the German PHQ-15 in a PC sample were deemed satisfactory [61].

Primary Care Post Traumatic Stress Disorder-5 (PC-PTSD-5): The PC-PTSD-5 [62] evaluates post-traumatic stress symptoms in the last 30 days with five dichotomous items (occurrence: “yes”/”no”). The total score can range from 0 (= no post-traumatic stress) to 5 and a score of 3 has been set as a psychopathological threshold. In a PC sample, the PC-PTSD, consisting of the first four items of the PC-PTSD-5, demonstrated good test–retest reliability (r = 0.83) and predictive validity [63].

##### Transdiagnostic outcomes

Emotion Beliefs Questionnaire (EBQ): The EBQ [64] measures affective mentalisation which entails the perceived controllability and usefulness of positive and negative emotions, and thus corresponds with the content of the first session of the transdiagnostic intervention. The EBQ comprises 16 items rated on a 7-point Likert scale (1: “strongly disagree” to 7: “strongly agree”). Eight items measure “general-controllability”, four items each examine “negative-usefulness” and “positive-usefulness”. The sum score can vary between 16 and 112, with higher values indicating that positive and negative emotions are perceived as less controllable and more useless. In a German non-clinical sample, the EBQ showed satisfactory internal consistency (α = 0.87), as did the subscales (general controllability: α = 0.85; negative-usefulness: α = 0.76; positive-usefulness: α = 0.70). Convergent and discriminant validity were also demonstrated [65].

Emotion Regulation Questionnaire (ERQ): The ERQ [66] assesses emotion regulation with ten items, of which four items measure emotion suppression and six items cover cognitive reappraisal. Emotion regulation is the primary skill targeted in the transdiagnostic intervention, with the reappraisal subscale closely aligning with the content of the second session. All items of the ERQ are rated on a 7-point Likert scale (1: “strongly disagree” to 7: “strongly agree”). Total scores on the suppression and reappraisal subscales can range from 4 to 28 and 6 to 42, respectively. Higher values on each subscale indicate a greater preference for suppression or reappraisal. The German ERQ reached satisfactory internal consistency for both the suppression (α = 0.74) and reappraisal (α = 0.76) subscale in a sample of medical students. Further, convergent and discriminant validity were indicated [67].

Brief Experiential Avoidance Questionnaire (BEAQ): The BEAQ [68] comprises 15 items rated on a 6-point Likert scale (1: “strongly disagree” to 6: “strongly agree”). It matches the content of the third session of the transdiagnostic intervention as it measures a tendency towards emotion-based avoidance. A higher overall score, varying between 15 and 90, suggests a greater extent of experiential avoidance. With the German BEAQ, five dimensions of experiential avoidance can be monitored: behavioural avoidance, distress aversion, procrastination, distraction/suppression and repression/denial. In a mixed sample of students and outpatients, the BEAQ yielded satisfactory internal consistency (α = 0.80) and test–retest reliability (r = 0.77). Discriminant and convergent validity were also shown [69].

Modified Personality Inventory for DSM-5 Brief Form (PID-5-BF + M): The PID-5-BF + M [70] assesses the personality traits of psychoticism, disinhibition, detachment, antagonism, anankastia and negative affectivity. Only the latter subscale will be employed in the pilot study, as negative affectivity (i.e., neuroticism) is the core transdiagnostic concept upon which the UP was developed [71]. Negative affectivity is measured with six items on a 4-point Likert scale (0: “very false or often false” to 3: “very true or often true”). Ranging between 0 and 18, a higher subscale score suggests greater negative affectivity. Norm values for the PID-5-BF + M were established for the German population [72]. In a PC sample, satisfactory reliability scores (α = 0.68—0.81) as well as convergent and discriminant validity were observed [73].

Kessler Psychological Distress Scale-6 (K-6): The K-6 [47] comprises 6 items that examine psychological distress over the last 30 days. Responses are given on a 5-point Likert scale (0: “none of the time” to 4: “all of the time”). The total score can range from 0 (no psychological distress) to 24, with higher values suggesting more distress. Commonly used in the PC setting [74], the K-6 will only be administered at t_0_ to complement GPs’ judgment of a patient’s psychological distress level. Established age-specific norm values for the German population will be provided to GPs [48]. The German Kessler-10, a longer version of the K-6 with four additional items, was found to have high internal consistency (students: α = 0.80; outpatients: α = 0.90) as well as satisfactory convergent validity [75].

#### Additional outcomes

At baseline (t_0_), socio-demographic data (i.e., age, sex, nationality, material status, highest educational level, current employment status, previous psychiatric diagnosis and corresponding treatment) will be assessed from patients. Patients’ medication intake will be recorded at t_0_ and t_1_. Also, at t_1_, the quality of treatment received for chronic illnesses of patients over the last 6 months will be examined, if applicable. For this, the Patient Assessment of Chronic Illness Care (PACIC) short form [76] will be used, which consists of 11 items rated on a 4-point percentage scale (0–25% to 76–100%). Over the course of the treatment period, GPs will document the number of patients approached for the study as well as treatment fidelity, any serious adverse events and reasons for study withdrawal of recruited patients. Among GPs, socio-demographic (i.e., age, sex) and occupation-related data (i.e., work experience, additional training, certain characteristics of their practice) will be collected post treatment (t_2_).

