#### Recruitment

PC practices will be recruited through the teaching practice network of the Institute of General Practice at LMU Munich and with flyers sent to GPs registered with the “Kassenärztliche Vereinigung” and/or the “Bayerische Landesärztekammer”. After a GP declares their interest to participate, inclusion criteria for GPs will be confirmed in a telephone call. If a GP meets the inclusion criteria, an appointment will be scheduled in which a member of study staff will visit the practice to explain all treatment details and the procedure of the study as well as to obtain informed consent (t_-1_).

GPs will recruit study participants from their pool of new and on-going patients. The identification of patients with a mental health condition will be based on a GP’s overall impression of a patient, assisted by a short questionnaire on general psychological distress (i.e., K-6 [47]). For the latter, GPs are provided with age-specific German norm values for the K-6 [48]. Eligibility will be confirmed by GPs with a checklist, covering all inclusion and exclusion criteria.

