#### Randomisation

Once at least one GP of a PC practice agrees to participate, cluster randomisation will be conducted at practice level as per a computer-generated sequence in a 1:1 ratio. This approach was chosen to prevent spillover effects within clusters, such as when several GPs from one practice participate in the study [49]. To ensure an even distribution of patients between IG and CG, randomisation will be stratified by the number of GPs in a practice providing treatment, assuming that practices with more participating GPs will treat more patients. As part of the consecutive recruitment, for each practice stratum (e.g., two participating GPs per practice), the first practice recruited is randomly allocated to either the IG or CG using the RANDBETWEEN function in Microsoft Excel [50]. This function generates an integer within a specified range (e.g., 1 or 2), with each value having an equal probability of being selected, thereby ensuring fairness in allocation. Within one stratum, the next recruited practice will be assigned to the opposite study group, and so forth. If a study group is underrepresented when a stratum is newly formed (i.e., more practices have been assigned to either study group overall), this study group will be prioritised for allocation to prevent imbalance in the distribution of practices.

Randomisation will be managed and documented by a staff member of the Institute of General Practice at LMU Munich, who is not part of the study [50]. Allocation concealment will be maintained using opaque envelopes, which will be opened by study staff only shortly before GPs are trained in their assigned treatment condition.

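### Apart from the stratum and the eligibility check, GP and practice characteristics are first collected at t2, so they may be missing for randomised practices that do not reach or answer that survey

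*Protocol article*

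**What the plan says.** Four sections of the protocol article fix when GPs supply data.

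- **Design:** "Data collection will take place at baseline (patients only) and after treatment completion (patients and GPs". GPs give no questionnaire data at baseline.
- **Procedure:** "Once the treatment of all patients is completed, GPs will be invited to fill in a digital questionnaire". This survey is t2. **Outcomes** repeats the timing: "GPs will be surveyed after completion of all treatments".
- **Additional outcomes:** GPs' age and sex, work experience, further training and "certain characteristics of their practice) will be collected post treatment", labelled t2.

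Randomisation comes much earlier. Under **Randomisation**: "Once at least one GP of a PC practice agrees to participate, cluster randomisation will be conducted at practice level". Two practice-level or GP-level facts are known by then. One is the stratum, since "randomisation will be stratified by the number of GPs in a practice providing treatment". The other is the GP's qualification in psychosomatic care or psychiatric training, because "inclusion criteria for GPs will be confirmed in a telephone call" (**Recruitment**). The same section describes a contact at t-1 in which "a member of study staff will visit the practice to explain all treatment details" and consent is taken.

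**Statistical analysis** lists practice characteristics among the descriptive statistics to be reported.

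**The concern.** Age, experience, training and practice features describe the randomised unit as it stood at allocation. The plan measures them at its last time point, on an invited form that follows completed treatment. The practices least likely to reach or answer that form are those that stopped, recruited nobody or lost interest. In a pilot whose primary aim is feasibility, including recruitment and delivery, they are also the most informative.

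Two uses are exposed. The first is the description of recruited practices by arm, which with about 10 practices per arm changes visibly if even one or two are absent. The second is the comparison of GPs who answered t2 with those who did not. GP feasibility and acceptability ratings are primary outcomes and come from the same survey, so a GP who does not answer loses both the ratings and most of the descriptors needed to judge who is missing. GPs know their allocation, and the arms ask different things of them: a structured flipchart programme in one, guideline-oriented sessions without further structure in the other. Loss that differs by arm is therefore plausible.

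**Working it through.** The plan gives no figure on this point, so there is none to reproduce. The check is mainly a reading of the sections in time order.

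**Step 1. What is known about a randomised practice, and when**

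| Time | Information | Section |
|---|---|---|
| Before allocation is revealed | Qualifying training of the GP; number of participating GPs | Recruitment; Randomisation |
| t0 | Patient baseline questionnaire, if the practice enrols anyone | Procedure; Additional outcomes |
| During treatment | Number of patients approached, fidelity, serious adverse events, reasons for patients' withdrawal | Additional outcomes |
| t2 | GP age, sex, experience, further training, practice characteristics; GP feasibility and acceptability ratings | Additional outcomes; Primary outcome measures |

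Everything in the last row depends on the GP reaching and answering one survey. No section gives another route to those items.

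**Step 2. What triggers t2**

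The trigger is completed treatment of all patients. This could mean the practice's own patients or those of the whole study. On either reading, a practice that withdraws or recruits nobody has no clear place in the sequence. The text neither excludes it from t2 nor says how it is invited. The payment of 100€ per recruited patient (Procedure) gives a practice without recruits nothing from that source.

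**Step 3. Scale, under assumption**

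Inputs: 20 practices (Sample size). The 20% dropout stated there is the allowance made for the patient sample; no loss rate for practices is given. Let q be the assumed probability that a practice has no t2 descriptors, independent between practices.

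- Expected number without descriptors = 20 × q
- Probability of at least one = 1 − (1 − q)^20

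| q (assumed) | Expected number of 20 | P(at least one) |
|---|---|---|
| 0.05 | 1 | 0.64 |
| 0.10 | 2 | 0.88 |
| 0.20 | 4 | 0.99 |
| 0.30 | 6 | >0.99 |

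Some gap is more likely than not even at 5% loss. The split by arm cannot be derived: an equal split would be a further assumption, and unequal loss is the case of most interest.

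**Step 4. What depends on these items**

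The mixed models contain treatment group, time, their interaction, and practice as the random component. No GP or practice descriptor is a covariate. The planned use is descriptive.

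**The case against.** A reader might infer that practices lost before t2 have no baseline data at all. The article does not support that. The stratum and the qualifying training are known for every randomised practice. A practice that enrolled patients before withdrawing has their t0 data. The documentation sheet is meant to record patients approached and fidelity without waiting for t2.

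A reader might also infer that failed practices are shut out of t2. No section says so. The institute holds GPs' contact data from the consent process and could still ask. That loss is an inference from the stated trigger and the absence of another route.

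Third, late collection hardly distorts the values. Sex is fixed, age and experience can be calculated back, and practice features should change little over a 12-week treatment. The idea that answers on further training are altered by taking part is speculative: the qualifying training was checked beforehand, and nothing suggests that the two-hour study training would be counted.

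Fourth, these are additional outcomes used for description, and moving them would not recover the missing GP ratings, which are the larger loss.

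All four arguments stand and limit the point. None removes it: the only stated collection time for most descriptors is the one most exposed to non-response. Because the ratings are lost with the same survey, descriptors taken earlier would be what is left to characterise the non-responders.

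**Conclusion.** The point holds as a minor one. Apart from the stratum and the qualification checked at eligibility, no GP or practice characteristics are planned before t2. They are therefore at risk of being missing for randomised practices that withdraw, recruit nobody or do not answer. The description of recruited practices, and any comparison of t2 responders with non-responders, could then rest on a selected subset.

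The size is unknown because the article gives no practice loss rate; the range of 1 to 6 practices of 20 rests entirely on the assumed 5% to 30% and on independence between practices. The harm is missingness, not measurement error. It would be wrong to infer that the estimated treatment effects are affected, since the models do not use these items.

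**What to change.** - Collect the GP and practice characteristics from every participating GP at the t-1 consent visit, before the allocation envelope is opened. The t-1 label also covers the training, so the text should name the consent visit.
- Keep the feasibility and acceptability items at t2.
- Send practices already enrolled a one-off short form now. Recruitment began in June 2024, so their answers come after allocation and should be reported as such.
- Use a GP-level code where a practice has several GPs. Data collection and management assigns one code per practice, which cannot link an individual GP's early answers to that GP's t2 ratings.
- Describe all randomised practices by arm, including those that did not recruit or finish, and state how many answered t2.

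The cost is one short form and a GP-level code. No outcome, sample size or model changes.
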